## Abstract

**Background:**

Polycystic ovary syndrome (PCOS), an incidence of 10–15% in women of reproductive age, shows sex hormone disorders, luteal insufficiency, and the tendency of placental villus space thrombus. The incidence of early pregnancy loss in women with PCOS is three to eight times higher than that in non-PCOS women. PCOS women were reported in a pre-thrombotic state, which was manifested by accelerated thrombin production, increased PAI-1 activity, and fibrinogen. Other research also found an over-activated state of women with PCOS in immune system. Therefore, changing the prethrombotic state of PCOS through anticoagulation may be a new way to improve the adverse pregnancy outcome of PCOS. Low-molecular-weight heparin (LMWH) is the most common used anticoagulant drug in pregnancy, and it also was proposed for the prevention of recurrent abortion, although the application of LMWH in PCOS population during early pregnancy has not been reported. The objective of this study is to investigate the effect of LMWH on pregnancy outcomes after invitro fertilization-frozen embryo transfer (IVF-FET) in patients with polycystic ovary syndrome.

**Methods:**

A total of 356 PCOS women aged between 20 and 38 years which prepared for IVF followed with FET will be enrolled in the study. The patients, from four different hospitals stratified by age and body mass index (BMI), will be randomly divided into the study group who will be treated with LMWH started on the day of progesterone transformation (hormone therapy) during FET cycle and the control group without additional medicine. Serum or urine hCG test will be given 14 days after embryo transfer to confirm biochemical pregnancy. If pregnancy is positive, LMWH+ hormone therapy/hormone therapy will be continued for another 2 weeks. Transvaginal ultrasonography will be performed 14 days later to confirm intrauterine pregnancy. The primary outcome is the ongoing pregnancy, which is defined as intrauterine live fetus with ultrasound after 12 weeks of gestation.

**Discussion:**

This is the first study protocol to investigate the efficacy of LMWH as an adjuvant drug for IVF-FET outcomes in PCOS women, by comparing differences in ongoing pregnancy rate, clinical pregnancy rate, live birth rate, and early pregnancy loss rate between LMWH group and the control group.

**Trial registration:**

ClinicalTrials.gov ChiCTR2000036527. Registered on August 24, 2020

**Supplementary Information:**

The online version contains supplementary material available at 10.1186/s13063-023-07877-x.

## Background

Polycystic ovary syndrome (PCOS) is one of the most common endocrine disorders in women of reproductive age, characterized by androgen hyperplasia, anovulation, and polycystic ovary, with an incidence of 9–18% during reproductive-aged women [1, 2]. In addition to the mechanism of ovulation disorder, PCOS patients also have the problem of poor endometrial receptivity. Regardless of natural or assisted conception, early pregnancy loss is pervasively among PCOS patients, 3–8 times higher than that of non-PCOS [3]. Adverse pregnancy outcomes not only cause great psychological and physiological harm to patients but also increase the social and economic burden. Therefore, what kind of intervention can improve pregnancy outcomes of PCOS patients has become the urgent task to be solved.

With more attention paid to the high incidence of cardiovascular diseases in PCOS patients, the disorder of coagulation system in PCOS patients has been proved in several studies. A pre-thrombotic state was proposed during PCOS women, which was manifested by increased activity of plasminogen activating inhibitor-1 (PAI-1) and fibrinogen. As a major inhibitor of fibrinolysis, the increase of PAI-1 is associated with low fibrinolysis, suggesting a high risk of thrombosis, while the increase of fibrinogen increases fibrin formation, plasma viscosity, and platelet aggregation, leading to hypercoagulability [4]. Low sex hormone-binding globulin (SHBG) and high insulin may partly explain the body mass index (BMI) independent difference of PAI-1 activity between women with PCOS and control group. It was also reported that the thrombin production rate of PCOS women was faster than that of non-PCOS ones, suggesting a higher risk of thrombosis [5]. Other researchers suggested that PCOS was an autoimmune disease [6], which was associated with a variety of autoimmune diseases, such as systemic lupus erythematosus and Hashimoto’s thyroiditis. Women with PCOS were proved to be involved in increased antibody levels, including antinuclear antibodies, antithyroid antibodies, anti-smooth muscle, anti-histone and anti-double-stranded DNA antibodies, also overactivation of the immune system, and pathophysiology of varying degrees of vascular endothelial damage. It is well known microthrombus formation in uterine embryo and placental circulation is closely related to pregnancy loss including RSA, fetal growth restriction, gestational hypertension, placental abruption, and stillbirth [7]. Therefore, changing the prethrombotic state of PCOS through anticoagulation may provide a new idea for improving pregnancy outcomes of PCOS.

Low-molecular-weight heparin (LMWH) is a glucosaminoglycan with 12~18 sugar units and an average relative molecular weight of 4000~5000, which is produced by enzymatic or chemical depolymerization of ordinary heparin. By binding with antithrombin III (AT-III), LMWH inhibits the activity of thrombin factor Xa and quickly suppresses thrombin formation, achieving anticoagulant effect. Its advantages include of little effect on platelets, rarely causing bleeding tendency, not passing through placenta, no secretion in milk, etc., belonging to FDA: Class B drugs (no reports of fetal malformation have been found). Therefore, it is the preferred anticoagulant drug in pregnancy at present. According to expert consensus published in 2018, LMWH is an effective drug for the treatment of recurrent spontaneous abortion (RSA) caused by antiphospholipid syndrome (APS), prethrombotic state (PTS), and autoimmune diseases [8, 9]. In recent years, some scholars have proposed the application of low-molecular-weight heparin to prevent recurrent abortion. Studies have supported the use of LMWH to increase live birth rate over aspirin in patients with unexplained recurrent pregnancy loss at risk for thrombosis [10, 11]. However, subsequent case-randomized controlled studies suggested that LMWH therapy did not improve unexplained recurrent abortion [12, 13]. Those conflicting results may owe to the heterogeneity of the coagulation status of the subjects and the diversity of the causes of abortion.

In addition, studies have shown other functions of LMWH, including immune regulation, promoting proliferation, invasion, and differentiation of trophoblast cells, inhibiting apoptosis of trophoblast cells, protecting vascular endothelium, and promoting placenta formation.

In conclusion, it is speculated that for PCOS infertility women with prethrombotic state and associated immune dysfunction, LMWH may improve membrane microcirculation during peri-implantation and enhance embryos development*.* However, so far, there are limited data for the administration of LMWH for in vitro fertilization frozen embryo transfer (FET) cycle in PCOS patients. Therefore, a randomized controlled trial is performed to prospectively evaluate the effect of LMWH on pregnancy outcomes of FET cycles, including ongoing pregnancy rate, clinical pregnancy rate, live birth rate, and early pregnancy loss rate.

## Methods

### Research design

This is an open-label randomized controlled superiority trial. Potentially eligible women will be given information about the study before invitro fertilization (IVF) treatment in four different tertiary hospitals: the International Peace Maternity and Child Health Hospital, Second Affiliated Hospital of Naval Medical University, the First Affiliated People’s Hospital of Wenzhou Medical University, and Taizhou Hospital of Zhejiang province. Training is uniformly conducted before the start of the trial to ensure the consistency of procedures in all the centers. The progress is periodically checked by professionals to ensure the uniformity and consistency. The sponsor of this trial is the International Peace Maternity and Child Health Hospital, School of Medicine, Shanghai Jiao Tong University. The research project was approved by the Ethics Committee of The International Peace Maternity and Child Health Hospital and was conducted according to the Declaration of Helsinki. The study was registered on ClinicalTrials.gov (no: ChiCTR2000036527).

The flow chart of this study is displayed in Fig. 1. A schedule of enrollment, interventions, and assessment is provided as Table 1.

**Fig. 1 Fig1:**
[figure not shown]
Flowchart of the study

**Table 1 Tab1:** Schedule of enrollment, interventions, and assessments

Unique form	Study period							
	Enrollment	Intervention phase		Follow-up				
		Ovarian stimulation	Frozen embryo transfer	2 weeks after FET	4 weeks after FET	10 weeks after FET	28 weeks of gestation	Perinatal period
Eligibility screen	𝙓							
Informed consent	𝙓							
Demographic characteristics	𝙓							
Medical/treatment history	𝙓							
Physical exam	𝙓							
Ultrasound	𝙓		𝙓	𝙓	𝙓			
Basic sex hormone	𝙓		𝙓	𝙓	𝙓			
Coagulation function assessment	𝙓		𝙓	𝙓	𝙓			
Safety test	𝙓							
IVF treatment		𝙓						
Randomization			𝙓					
Frozen embryo transfer			𝙓					
Pregnancy evaluation				𝙓	𝙓	𝙓	𝙓	
Perinatal data collection								𝙓

### Recruitment

Recruitment advertisements for the trial were posted on the official platforms of each participating institution. PCOS women undergoing IVF at any one of the four participating institutions will be screened for eligibility. The potential subjects who meet the enrollment criteria will be referred to investigators by their physician on the first day attending IVF department. This trial will be explained by a designated investigator in detail prior to signing informed consent. Written informed consent will be obtained before joining the trial. Participants can decline to join the trial or quit at any time without any consequences for their clinical treatments.

### Inclusion criteria

Patients who met the following inclusion criteria are included in the study:Chinese women aged between 20 and 38 yearsMeet Rotterdam PCOS standard diagnosisTwo of the following three criteria are met: (1) sparse ovulation or anovulation, (2) hyperandrogenemia or clinical manifestations of hyperandrogenism, and (3) ultrasonography performed on 3 to 5 days after bleeding during the menstrual cycle or after progesterone withdraw show both ovaries had ≥ 12 small follicles with a diameter of 2 to 9 mm and/or ovarian volume > 10 mL.No IVF historyWilling to cooperate with the research plan and sign the informed consent

### Exclusion criteria used in this study:

Other causes of hyperandrogenism, such as thyroid disease congenital adrenal cortical hyperplasiaA history of three or more miscarriages or combined with immunogenic infertilityComplicated with severe male infertility and immune infertilityThe presence of uterine lesions: Uterine malformation, adenomyosis, submucosal myoma, or uterine adhesionsPrior unilateral oophorectomyChromosomal abnormalities and need to undergo preimplantation genetic testing (PGT)Have contraindications to assisted reproductive technologyContraindications to drug use: Unexplained liver disease or abnormal liver function (abnormal serum liver enzyme indicators); kidney disease or abnormal renal function; severe anemia; history of deep vein thrombosis and pulmonary embolism history and history of cerebrovascular accident; diagnosed heart disease; a history of cervical, endometrial, or breast cancer; and vaginal bleeding of unknown cause

### Randomization and allocation concealment

PCOS women meeting the inclusion criteria will be recruited and randomized according to an online Central Randomization System stratified by the study sites and women’s age (35 years), supported by Shanghai Clinical Research Center, on the day of progesterone transformation. Participants are assigned in a 1:1 ratio randomly to the study group (LMWH + hormone therapy) or the control group (hormone therapy). LMWH is given daily subcutaneous starting from the progesterone transformation day. The dynamic block method is used to develop the randomization scheme, and the multicenter electronic random system is used to stratify the subjects within the block. Both investigators and participants are unblinded for the allocation of the intervention, while the biostatistician will be blinded to the group allocation.

### Sample size calculation

According to the previous data, the continuous pregnancy rate of female PCOS patients treated with LMWH within 1 week was 45%, while the continuous pregnancy rate of PCOS patients with IVF after routine pre-treatment was about 30%. According to the optimal efficacy experiment, *α* = 0.05, *β* = 0.20, and 10% loss of follow-up and shedding were set. According to the sample size formula, about 178 subjects in each group and 356 subjects should be recruited.

### Adherence

Participants are fully informed that the trial does not involve the increase blood test, and patient visits, as well as the safety and application of the intervention. The attending in charge system improves the relationship between clinicians and participants. Participants can consult the clinician in the clinic at each visit about the treatment regimen and adverse effects if any. Any trial-related questions or discomfort can be communicated with our clinical experts by WeChat platform, and participants can get advice on treatment.

### Interventions

Participants will be subjected to an antagonist regimen of controlled ovulation stimulation, egg extraction, and whole embryo cryopreservation. During the FET cycle, the endometrium will be prepared by hormone therapy. As endometrium thickness is above 8 mm, progesterone will be added preparing for embryos transfer. Clexane 4000 IU (0.4 mL) is given injected daily from the progesterone transformation until hCG determination showing negative or transvaginal ultrasound verifying the presence of intrauterine pregnancy.

Concomitant treatments of immunosuppressants and other drugs that alter blood coagulation condition, such as hydroxychloroquine and warfarin sodium, are not permitted during the trial.

### Outcome measures

The primary outcome will be the ongoing pregnancy rate resulting from the FET cycles, which is defined by the presence of a gestational sac with a fetal heartbeat after 12 weeks of gestation. Secondary outcomes include live birth rate, preterm delivery, pregnancy complications, and early pregnancy loss rate. Live birth rate is defined as the percentage of birth cycles with at least one surviving birth to transplant cycles in the number of transplant cycles. Preterm delivery is defined as a delivery of gestational age of less than 37 weeks. Pregnancy complications mainly refer as preeclampsia (PE) and gestational diabetes (GDM). PE is defined by the combination of gestational hypertension and proteinuria occurring after 20 weeks of gestation. GDM is made when any of the following plasma glucose values are met or exceeded: (1) fasting: 92 mg/dL (5.1 mmol/L); (2) 1 h: 180 mg/dL (10.0 mmol/L); and (3) 2 h: 153 mg/dL (8.5 mmol/L). Early pregnancy loss is defined as loss of the embryo before 12 weeks of gestation, and early pregnancy loss rate refers to the percentage of early pregnancy loss cycles in the number of clinic pregnancy cycles.

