## Discussion

To our knowledge, this is the first study protocol to investigate the efficacy of LMWH as an adjuvant drug for IVF-FET outcomes in PCOS women. PCOS is one of the most important causes of female infertility. Increased risk of embryo implantation failure and early embryo loss rates were revealed by previous studies in patients with PCOS. Hypercoagulability and prethrombotic state might contribute to in PCOS patients’ pregnancy loss. LMWH preventative treatment was empirically used in RSA patients and partly showed positive results.

Our retrospective case-control study showed that significant higher clinic pregnancy rate and livebirth rate in LMWH group (supplemented with LMWH from the day of progesterone transformation) compared with those of control group. LMWH treatment seems to reduce the early pregnancy loss in IVF-FET. Therefore, it is speculated that for PCOS infertility women with prethrombotic state and associated immune dysfunction, LMWH may help to improve membrane microcirculation during peri-implantation and enhance embryos development. However, so far, there are limited data for the administration of LMWH for FET cycle in PCOS patients. Therefore, a randomized controlled trial is designed to prospectively evaluate the effect of LMWH on the IVF outcomes of FET cycles, including ongoing pregnancy rate, clinical pregnancy rate, live birth rate, and early pregnancy loss rate.

The strengths of the present study include that this is a multicenter, central dynamic randomized trial. Age, BMI, and subcenters were designed as block factors for minimizing bias. There are also some limitations: For LMWH is given subcutaneous, although good adherence in patients, it is not suitable for blind design. The nature of the LMWH treatment is open to treating physicians but blind to embryologists, laboratory technicians, and follow-ups of this study; the study population is Han of ethnic, and further studies are necessary to verify our conclusions correction in other ethnic populations, with varied genotype and phenotype.

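### The early pregnancy loss rate starts at about the scan that ends LMWH, so losses between a positive hCG and that scan are not counted as early losses

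*Protocol article*

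**What the plan says.** Outcome measures in the protocol article gives the event, "Early pregnancy loss is defined as loss of the embryo before 12 weeks of gestation", and then the rate: "early pregnancy loss rate refers to the percentage of early pregnancy loss cycles in the number of clinic pregnancy cycles". The event has no lower time limit. Clinical pregnancy is not defined there or elsewhere in the article.

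The timeline comes from three places:

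- Randomization and allocation concealment: women are randomised "on the day of progesterone transformation", and LMWH starts that day, before transfer.
- Abstract, Methods: "Serum or urine hCG test will be given 14 days after embryo transfer to confirm biochemical pregnancy". Then: "If pregnancy is positive, LMWH+ hormone therapy/hormone therapy will be continued for another 2 weeks". Then: "Transvaginal ultrasonography will be performed 14 days later to confirm intrauterine pregnancy".
- Interventions: LMWH is given "until hCG determination showing negative or transvaginal ultrasound verifying the presence of intrauterine pregnancy".

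The Abstract, Background and Discussion all name the early pregnancy loss rate among the outcomes to be compared. The Discussion reports from the group's own retrospective study that "LMWH treatment seems to reduce the early pregnancy loss in IVF-FET".

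**The concern.** The scan that appears to admit a woman to the denominator is the scan at which LMWH stops. A pregnancy that is hCG-positive at week 2 and has disappeared by week 4 was lost while LMWH was due, yet it does not enter the early-loss rate. No other listed outcome records it as a loss.

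Two things follow. First, the outcome named for early loss says little about losses during treatment, although the Background and Discussion place the hoped-for benefit around implantation. Second, the women in the denominator are selected after randomisation. If LMWH changes which pregnancies survive to the scan, the two sets of clinical pregnancies are no longer comparable by randomisation. The trial could then report no difference in early loss even though LMWH had reduced it.

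**Working it through.** **Plan's own figures.** The article gives no rate for early loss, so there is nothing to reproduce on this point. The only related figure is the sample size: n = (1.96 + 0.84)² × (0.30×0.70 + 0.45×0.55) / 0.15² ≈ 160 per arm, and 160/0.90 ≈ 178. It matches the stated 178 and is not affected.

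**Timeline.** hCG test at day 14 after transfer. Confirming scan 14 days later: 14 + 14 = 28 days, or week 4. LMWH covers the whole interval and ends when the scan verifies an intrauterine pregnancy. That scan defines clinical pregnancy only by inference, but no other scan is described as confirming pregnancy.

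**Where one woman is counted** (hCG-positive at week 2, nothing visible at week 4):

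| Listed outcome | How she counts |
|---|---|
| Ongoing pregnancy (primary) | failure |
| Live birth per transfer cycle | failure |
| Early pregnancy loss per clinical pregnancy | not in the denominator |

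In the first two she cannot be told apart from a woman who never had a positive hCG.

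**Illustration.** All inputs are assumptions, not document figures:

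- b = proportion of hCG-positive pregnancies lost before the scan in the control arm: 20% (range 10–30%)
- LMWH halves this to b/2
- loss from scan to 12 weeks: 25% of clinical pregnancies in both arms
- hCG-positive rate equal in both arms

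Per hCG-positive woman:

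- Control: clinical pregnancies 1 − b; all loss = b + 0.25(1 − b)
- LMWH: clinical pregnancies 1 − b/2; all loss = b/2 + 0.25(1 − b/2)
- Rate as defined: 0.25 in both arms, whatever b is

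| b | As defined, control vs LMWH | All loss per positive hCG, control vs LMWH | RR, all loss |
|---|---|---|---|
| 10% | 25% vs 25% | 32.5% vs 28.75% | 0.88 |
| 20% | 25% vs 25% | 40% vs 32.5% | 0.81 |
| 30% | 25% vs 25% | 47.5% vs 36.25% | 0.76 |

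Share of control-arm losses outside the defined rate: 0.10/0.325 = 31%, 0.20/0.40 = 50%, 0.30/0.475 = 63%. With an assumed 50% hCG-positive, 178 × 0.50 = 89 control women, of whom 8.9 to 26.7 (about 9 to 27) would have a loss not counted as such.

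**Compatibility with the planning rate.** With 50% hCG-positive and b = 20%, control ongoing pregnancy is 0.50 × (1 − 0.40) = 30%, the control rate used for the sample size. This makes the inputs compatible with the plan but does not establish them. Other combinations also give 30%.

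**Same case per randomised woman.** Total loss 0.50 × 0.40 = 20% vs 0.50 × 0.325 = 16.25%. Ongoing pregnancy 30% vs 0.50 × 0.675 = 33.75%. So the primary outcome does register the benefit.

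**The case against.** The other side has several good points.

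- **A reader might infer that these losses vanish from the trial.** They do not. Each is a failure in the primary outcome and in live birth per transfer cycle, with analysis by intention to treat. What is lost is their identification as early losses, in one secondary outcome for which the trial was not sized.
- **A reader might infer that every loss on treatment is missed.** The article does not support this. The scan verifies an intrauterine pregnancy, not a live embryo. If a visible sac is enough for clinical pregnancy, an embryo that stopped developing before the scan would still be counted. Only pregnancies gone or not visible fall outside.
- **A reader might infer that the numerator can hold women absent from the denominator, so that the ratio is no proportion and the log-binomial model fails.** The event has no lower time limit, so the wording is loose. But a percentage of clinical pregnancy cycles is most naturally read as a subset, and the Abstract separates biochemical from intrauterine pregnancy.
- **A reader might infer that the defined rate would point the wrong way.** That needs pregnancies saved on LMWH to have a higher later loss. At an assumed 50%, the LMWH rate is (0.25×0.80 + 0.50×0.10)/0.90 = 27.8%, RR 1.11. Nothing in the document supports that input.
- **Loss per clinical pregnancy is a legitimate question.** The Background also cites trophoblast and placental effects, which could act after dosing ends. This is a good reason to keep the listed rate.
- **Starting at the positive hCG still conditions on an event after randomisation**, because LMWH begins before transfer. This stands, and it is why the comparison should be per randomised woman.

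What remains is that the listed rate mainly covers the period after LMWH, and nothing listed reports the earlier losses as losses.

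**Conclusion.** The point holds for the early pregnancy loss outcome only. On the natural reading, its rate begins at about the end of LMWH and is taken in a subset that LMWH may change. It could show no difference even if LMWH reduced losses during treatment. The conclusion depends on one inference: that clinical pregnancy is established at the week-4 scan.

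The size cannot be fixed from the document. The contrast of 25% vs 25% as defined against 40% vs 32.5% per positive hCG (RR 0.81, range 0.88 to 0.76) shows what is possible under assumed rates and is not a forecast. The primary outcome and the sample size stand. The weakness matters because early loss is a named objective, and a null result on it could be misread as no effect on early loss.

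**What to change.** In Outcome measures:

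1. Define clinical pregnancy by the week-4 scan, stating what must be seen. Keep the rate per clinical pregnancy as listed.
2. Add a pre-specified total early pregnancy loss outcome, from the positive hCG 14 days after transfer to 12 weeks, split into loss before the week-4 scan and loss from the scan to 12 weeks.
3. Report it per randomised woman as the randomised comparison, and per hCG-positive woman as description.
4. Show hCG-positive and ongoing pregnancy per randomised woman beside it. Loss per randomised woman can mislead alone: if LMWH also raised hCG-positive from 50% to an assumed 60%, loss would be 20% vs 0.60 × 0.325 = 19.5%, while ongoing pregnancy would be 30% vs 0.60 × 0.675 = 40.5%.
5. List ectopic pregnancy, termination and loss to follow-up separately, and do not count them as early losses.

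The cost is small: an amendment and one or two table rows. The week-2 and week-4 evaluations are already in Table 1, so no visit is added. Loss before the scan depends on whether hCG was measured in serum or urine, so the assay should be recorded. Recruitment to this open-label trial began in March 2021, so the amendment should be dated and settled before any comparison by arm. No change to treatment is implied.

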### Statistical analysis

The study data are collected and managed by nonclinical staff who are responsible for data management in each clinical center. In case of missing values of baseline characteristics, we will analyze them by excluding the missing values, then assign the missing values multiple times, and conduct subsequent analyses to estimate the robustness of the results. For follow-up loss and protocol violation, we will attempt sensitivity analysis to explore the influence of these factors on the trial results.

Baseline characteristics will be described by descriptive analysis, and the balance among groups or subgroups will be assessed by analysis for different kinds of data. Continuous variables with normal distribution are presented as means with standard deviations (SDs) and continuous variables non-normally distributed as medians and interquartile ranges (IQRs). Categorical variables are presented in the form of *n* (%). The result will be analyzed according to the intention-to-treat (ITT) principle. The primary outcome (the ongoing pregnancy rate) and categorical secondary outcomes will be compared between groups by means of log-binomial regression. Adjusted risk ratios (aRRs) and unadjusted risk ratios (RRs), as well as their associated 95% confidence intervals (CIs), will be presented. And the 95% CI of the absolute rate differences (ARDs) will be used to evaluate if the LMWH group is superior to the control group. Continuous data with normal distribution will be analyzed using a two-sample *t*-test, and the Mann-Whitney *U*-test will be used for non-normally distributed data. Subgroup analysis is planned in cases categorized by year (≥ 35 years, < 35 years) and BMI (< 25, ≥ 25). To test the potential interaction between subgroups and treatment effect, we will fit a model with fixed effects to compare the treatment arms with respect to the primary outcome of the ongoing pregnancy rate and binary secondary outcomes (e.g., rates of live birth, preterm delivery, pregnancy complications, and early pregnancy loss). Statistics will be run using SPSS version 21 software (SPSS, Inc., Chicago, IL, USA). *P*-values of less than 0.05 were considered to be statistically significant.

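### Early pregnancy loss per clinical pregnancy, and to a lesser degree live birth per transfer, are compared between arms on denominators formed after randomisation, although ITT is claimed

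*Protocol article*

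**What the plan says.** All references are to the protocol article.

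- **Outcome measures**, early loss: "early pregnancy loss rate refers to the percentage of early pregnancy loss cycles in the number of clinic pregnancy cycles".
- **Outcome measures**, live birth: "the percentage of birth cycles with at least one surviving birth to transplant cycles in the number of transplant cycles".
- **Randomization and allocation concealment**: women are randomised "on the day of progesterone transformation", and "LMWH is given daily subcutaneous starting from the progesterone transformation day". Under Interventions, progesterone is added in preparation for transfer, so transfer comes later.
- **Statistical analysis**: "The result will be analyzed according to the intention-to-treat (ITT) principle". No exception is made for secondary outcomes. Those that are categorical go through the same log-binomial model as the primary outcome, with risk ratios and 95% confidence intervals.
- **Discussion**: the sponsor's retrospective study found "significant higher clinic pregnancy rate and livebirth rate in LMWH group", and the proposed mechanism acts around implantation.

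The article gives no version of either outcome per randomised woman, and it does not call the rate per clinical pregnancy descriptive. Clinical pregnancy is promised as a compared outcome in the Abstract, at the end of the Background and in the Discussion, but Outcome measures does not list it.

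**The concern.** Randomisation makes the arms comparable on the progesterone day. A woman enters the early-loss denominator only if she later has a clinical pregnancy, after LMWH has started and possibly because of it. If LMWH changes who becomes pregnant, the pregnancies in the two arms are of different kinds. A difference in loss per pregnancy then mixes any effect on loss with a change in who is counted.

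This matters because early loss is central to the rationale in the Abstract and Background, and the Discussion already suggests that LMWH lowers it. The planned comparison could appear to support that with no fewer losses among the women randomised, or could hide a difference in losses.

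The live-birth rate per transfer has a milder form of the same fault: a randomised woman without a transfer drops out.

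**Working it through.** **Inputs from the article (Sample size calculation).** Ongoing pregnancy 30% in control and 45% with LMWH, α = 0.05, β = 0.20, 10% loss, 178 per group.

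**Inputs assumed.** The article gives no rate of clinical pregnancy, early loss or transfer completion. Every such figure below is an assumption.

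**1. The plan's own figure.** With unpooled variance and a two-sided test, n = (0.30×0.70 + 0.45×0.55) × (1.96 + 0.84)² / 0.15², rounded up to 160 per arm. Then 160 / (1 − 0.10) = 177.8, or 178. The stated figure reproduces, and this point does not touch it.

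**2. Planned rate against loss per randomised woman.** Here CP is clinical pregnancy and OP ongoing pregnancy, both as proportions of randomised women. Loss per woman = CP − OP. The planned rate = (CP − OP) / CP.

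| Assumed CP, control / LMWH | Loss per randomised woman | Planned rate | RR of planned rate |
|---|---|---|---|
| 40% / 55% | 10% / 10% | 0.10/0.40 = 25% / 0.10/0.55 = 18.2% | 0.73 |
| 40% / 60% | 10% / 15% | 0.10/0.40 = 25% / 0.15/0.60 = 25% | 1.00 |

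In the first row the planned rate falls although as many women per 100 randomised lose a pregnancy. In the second it shows no difference although losses per woman differ.

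**3. No effect on loss in women who would be pregnant in either arm.** Assume control CP of 37.5% with 20% lost, which returns the protocol's 30% ongoing (0.375 × 0.80). Let LMWH add pregnancies and leave loss unchanged in the rest. With *e* added pregnancies and loss *f* among them, the LMWH planned rate is (0.075 + e×f) / (0.375 + e).

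| e | f | LMWH loss per CP | RR against 20% | Ongoing, LMWH | Loss per randomised woman, LMWH (control 7.5%) |
|---|---|---|---|---|---|
| 10 points | 0% | 0.075/0.475 = 15.8% | 0.79 | 40% | 7.5% |
| 10 points | 60% | 0.135/0.475 = 28.4% | 1.42 | 34% | 13.5% |
| 15 points | 0% | 0.075/0.525 = 14.3% | 0.71 | 45% | 7.5% |
| 15 points | 60% | 0.165/0.525 = 31.4% | 1.57 | 36% | 16.5% |

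For e from 5 to 15 points and f from 0% to 60%, the RR runs from 0.71 to 1.57. Either direction can appear with no true effect on loss in women pregnant under both treatments.

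**4. Size of the compared subsets.** At the planned ongoing rates and an assumed 20% loss in both arms, the denominators are 178 × 0.30/0.80 ≈ 67 control women and 178 × 0.45/0.80 ≈ 100 LMWH women. That is 38% and 56% of those randomised.

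**5. Live birth.** If live birth per transfer is equal in both arms, the RR per randomised woman is the ratio of transfer completion. Assumed completion of 98% (control) against 95% (LMWH) gives 0.95/0.98 = 0.97, and 98% against 90% gives 0.92. The reverse, 90% against 98%, gives 1.09. Equal completion gives 1.00.

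**The case against.** - **Loss per clinical pregnancy is a familiar measure, and loss per randomised woman can mislead too.** This stands. In the 40% / 60% row, losses per woman go from 10% to 15% while ongoing pregnancy rises from 30% to 45%: more women conceive, so more can lose a pregnancy. The fault lies in comparing the conditional rate between arms as an ITT result, not in reporting it. Early loss per woman should not be read alone either.
- **The magnitudes rest on assumed rates.** True. They show that the planned rate cannot separate an effect on loss from a change in who conceives. They do not predict the trial's result. The 40% / 55% row could also arise if LMWH did prevent some losses, and the planned rate would not tell the two apart.
- **Live birth is hardly affected.** Largely right. On the progesterone day embryos are already frozen and the endometrium has reached the required thickness, so few women should go without a transfer.
- **The outcome list is introduced as inclusive and need not be complete.** That may explain why clinical pregnancy is missing. Since it is the early-loss denominator and is promised elsewhere, it should still be listed.

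Two stronger readings are tempting, and the documents do not support them. A reader might infer from the word cycles that one woman can contribute several transfers, analysed as if independent. But Table 1 has one randomisation and one transfer, with follow-up timed from that transfer, and nothing provides for repeats. A reader might also infer that the primary outcome, "the ongoing pregnancy rate resulting from the FET cycles", breaks ITT. That phrase says where the pregnancies arise and names no denominator, and the sample size counts subjects.

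**Conclusion.** The point holds for secondary outcomes only, as something that should be fixed. The early-loss comparison conditions on clinical pregnancy, which arises after treatment starts and which the sponsor's own data suggest LMWH changes. It is therefore not a randomised comparison and does not fit the stated ITT principle. Under the assumed rates, it can show an RR of 0.73 with equal losses per randomised woman, and between 0.71 and 1.57 with no effect on loss in women who would be pregnant in either arm.

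For live birth the departure from ITT is real but probably small: an RR factor of 0.92 to 1.09 if completion lies between 90% and 98% per arm, and none if it is equal.

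The order of randomisation, first dose and transfer, and both denominators, come from the article. The clinical pregnancy, loss and completion rates are assumptions.

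**What to change.** 1. For the ITT comparison, define live birth and early pregnancy loss per randomised woman. A woman with no transfer or no pregnancy counts as no live birth and no early loss.
2. Present early loss only beside clinical pregnancy, ongoing pregnancy and live birth, all per randomised woman, so that a rise in losses due only to more conceptions can be recognised.
3. Keep loss per clinical pregnancy and live birth per transfer as descriptive rates, without a superiority claim.
4. Add clinical pregnancy to Outcome measures, to match the Abstract, Background and Discussion.

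The cost is wording and tables, with no change to the sample size. If the sponsor treats it as a protocol amendment, it follows the ethics route described under Data collection and monitoring. The downside is that the live-birth rates will be slightly lower than conventional per-transfer rates, which the retained descriptive rates offset.
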